## Abstract

**Background:**

Adenomyosis is a benign uterine disease characterized by invasion of endometrium into the myometrium resulting in heavy menstrual bleeding and pain (dysmenorrhea). Hysterectomy is established as the final treatment option when conservative treatment fails. Uterine artery embolization (UAE) in patients with symptomatic adenomyosis has demonstrated to reduce symptoms and improve quality of life. However, randomized controlled trials are lacking.

**Objective:**

With this study, we aim to evaluate the impact of UAE on Health-Related Quality of Life (HRQOL) in a randomized comparison to hysterectomy in patients with symptomatic adenomyosis.

**Methods:**

This is a multicenter non-blinded randomized controlled trial comparing UAE and hysterectomy. Eligible patients are symptomatic premenopausal women without the desire to conceive and who have symptomatic magnetic resonance imaging (MRI)–confirmed pure adenomyosis or dominant adenomyosis accompanied by fibroids. After obtaining informed consent, patients will be randomly allocated to treatment in a 2:1 UAE versus hysterectomy ratio. The primary objective is HRQOL at 6 months following the assigned intervention. Secondary outcomes are technical results, pain management, clinical outcomes, HRQOL, and cost effectiveness during 2 years of follow-up. In addition, transvaginal ultrasound (TVUS) and MRI will be performed at regular intervals after UAE.

**Results:**

Patient enrollment started November 2015. The follow-up period will be completed two years after inclusion of the last patient. At the time of submission of this article, data cleaning and analyses have not yet started.

**Conclusions:**

This trial will provide insight for caretakers and future patients about the effect of UAE compared to the gold standard hysterectomy in the treatment of symptomatic adenomyosis and is therefore expected to improve patients’ wellbeing and quality of life.

**Trial Registration:**

Netherlands Trial Register NTR5615; http://www.trialregister.nl/trialreg/admin/rctview.asp?TC=5615 (Archived by WebCite at http://www.webcitation.org/6xZRyXeIF)

## Introduction

Adenomyosis is described as the benign presence of ectopic endometrial glands and stroma causing reactive hypertrophy of the smooth muscle fibers of the myometrium [1,2]. The prevalence of adenomyosis is estimated to be 5%-8% in some studies, whereas others find even 40%-70% [3-5]. Approximately one-third of women with adenomyosis are symptomatic [2]. Symptoms associated with the presence of adenomyosis are abnormal menstrual bleeding, pain (dysmenorrhea) and an enlarged uterus. About 40%-50% and 15%-30% of patients will suffer from heavy menstrual bleeding and/or dysmenorrhea, respectively [3]. Fibroids are present in up to 55% of the patients diagnosed with adenomyosis [6]. Therefore, it can be difficult attributing symptoms to one or the other [7,8]. Adenomyosis can be diagnosed with transvaginal ultrasonography (TVUS) or magnetic resonance imaging (MRI) [9,10]. Adenomyosis can be treated conservatively (hormonal/non-hormonal). When conservative management fails, a hysterectomy is the most common surgical solution, since surgical removal of adenomyosis is difficult given its diffuse aspect.

Uterine artery embolization (UAE) has been a minimally invasive treatment for symptomatic uterine fibroids since 1995 [11]. Since then, much research has been conducted including several randomized controlled trials establishing UAE as a valuable treatment option for women with symptomatic fibroids [12-14].

During the last fifteen years, several case series and cohorts evaluated UAE as a treatment for patients suffering from symptomatic adenomyosis. These cohorts show promising results [15-26]. Randomized data, comparing this new treatment modality with the gold standard (ie, hysterectomy) are lacking though. The “Quality of Life after Embolization vs Hysterectomy in Adenomyosis” (QUESTA) trial was set up to fill this knowledge gap comparing UAE with hysterectomy in patients with symptomatic adenomyosis. In this paper, we present the design of the trial.

## Methods

### Design

The QUESTA trial is a multicenter nonblinded randomized controlled trial, performed within selected hospitals in the Netherlands containing experienced interventional radiologists qualified to perform UAE. The study is performed in a network infrastructure in which radiologists and gynecologists collaborate. This trial will be conducted in accordance with the Consolidated Standard of Reporting Trials [27-29], the principles of the Declaration of Helsinki, and the Medical Research Involving Human Subject Act.

This study is approved by the ethics committee of the VU Medical Centre Amsterdam (Reference Number 2015/211) and by the boards of all participating hospitals. The trial is registered at the Netherlands Trial Registry (Netherlands Trial Register NTR5615).

### Participants and eligibility criteria

Eligible adult women are asked to participate when they meet the following inclusion criteria:

Premenopausal women with symptomatic pure adenomyosis or dominant adenomyosis (with concurrent uterine fibroids). Symptoms are defined as heavy menstrual bleeding, dysmenorrhea, and/or cycle independent pain and bulk-related symptoms.Women with an indication for hysterectomy. These women had or have unsuccessful medicinal treatment or decided that such treatment is no option.

The exclusion criteria are:

Patients younger than 18 years of agePatients with a pelvic infectionSuspicion or presence of a malignancyCurrent pregnancy or desire to conceive in the futureAbsolute contraindication for angiographyDeep infiltrating endometriosis requiring surgery or risks on intestinal stenosisConcurrent hysteroscopic removable submucous fibroids

### Procedures, recruitment, and randomization

When adenomyosis is suspected on TVUS (see criteria in Table 1) and MRI is performed to confirm adenomyosis (see criteria in Table 2), eligible patients will be informed about the study by the gynecologist, resident, research nurse or study coordinator and will be informed about the website for additional information and an introduction video (Multimedia Appendix 1). If the patient declines randomization, she will be asked to participate in the cohort group. The patients in the cohort study group will be offered standard care (ie, hysterectomy, since embolization is not available outside the trial). Afterwards, participants with written informed consent are randomly allocated (2:1) to the experimental intervention (UAE) or the standard care control group (hysterectomy). Randomization is computer-based and stratified for the participating hospitals. The study is not blinded since uterine artery embolization is performed either under conscious sedation or epidural anesthesia in contrast to a hysterectomy which is performed in the operating room under full narcosis. Therefore, it is not possible to blind the patients or the physicians.

### Intervention group

A specific UAE particle protocol for adenomyosis will be delivered to the interventional radiologist of each center and, if needed, our experienced interventional radiologist will be present during the first UAE procedure ([name]).

**Table 1 table1:** Criteria for diagnosing adenomyosis on transvaginal ultrasonography (TVUS).

Criteria	eCRF^a^ answers
Uterus (cm)	Height*length*width
Asymmetrical thickening^b^	Yes/no/I don’t know; Measurements uterine walls
Cysts^b^	Yes/no/I don’t know
Fan-shaped shadowing^b^	Yes/no/I don’t know
Myometrial aspect^b^	Homogenous/inhomogeneous/I don’t know
Inhomogeneous endometrial-myometrial zone (endometrial lines/buds)^b^	Yes/no/I don’t know
Diffuse flow^b^	Yes/no/I don’t know
Adenomyosis type	Diffuse/Focal/Combined diffuse>focal/Combined focal>diffuse
Fibroids	Yes/no/I don’t know
Fibroid count	Number
Size biggest fibroids (cm)	Height*length*width
Occurrence of pedunculated fibroid	Yes/no
Pedunculated fibroid count	Number

^a^eCRF:electronic clinical report forms.

^a^Adenomyosis criteria. If 3/6 are recognized, adenomyosis is suspected.

**Table 2 table2:** Criteria for diagnosing adenomyosis on magnetic resonance imaging (MRI).

Criteria and types	Definition
Adenomyosis	Junctional zone^a^>12mm diameter
Cysts (hyper intense foci T2)	Yes/no
Asymmetric myometria	Yes/no
Adenomyosis category 1	Focal: 25% or less of endometrial interface
Adenomyosis category 2	Regional: Entire endometrial surface of the anterior wall, posterior wall or fundus
Adenomyosis category 3	Diffuse: Entire or most of the endometrial surface Moderate: 20-29mm Severe: ≥30mm
Dominant adenomyosis in combination with fibroid	Volume domination: Adenomyosis>fibroids

^a^Adenomyosis is confirmed.

UAE is carried out under epidural anesthesia or patient controlled analgesia (PCA). A catheter is introduced in the femoral artery and positioned selectively into the uterine arteries under fluoroscopic guidance. Microspheres are then injected through the catheter into the uterine artery. The bloodstream will move the microspheres towards the small uterine artery branches in the area of adenomyosis (and fibroids if present). Microspheres consist of a hydrogel core with polymethylmethacrylate (PMMA) and a flexible shell of polyphosphazene (Polyzene-F), which is a synthesized inorganic biostable and biocompatible polymer (Embozene microsphere). This embolic agent establishes reduction and cessation of blood flow to the area of adenomyosis resulting in ischemia and infarction. The embolization protocol sets out the provisions regarding the microsphere size (Embozene 500 µm) for use and the angiographic embolization end-point until full stasis at the distal end of the uterine artery.

A second protocol will include: administration of antibiotics, drip infusions, Foley bladder catheters, PCA pump usage with strict protocols for pain management, and a nursing protocol for the ward.

### Control group

Hysterectomy is preferably performed by vaginal hysterectomy (VH) or total laparoscopic hysterectomy (TLH). A TLH or abdominal hysterectomy is always performed under general anesthesia. No protocol will be provided for surgical standardization. Adhesiolysis will be performed when necessary. Planned concomitant endometriosis surgery serves as an exclusion criterion. However, during surgery, coagulation of mild endometriosis is allowed. In case of laparoscopic or vaginal hysterectomy, the uterus will be removed vaginally or by the use of (in bag) morcellation. Supra cervical hysterectomy is allowed.

### Data collection

All electronic clinical report forms (eCRF) and patient questionnaires are digitally online secured and filled out in the study website with the use of a patient-specific study number [30]. The patient and physician receive this study number at time of informed consent. Figure 1 shows the study flowchart.

### Baseline

At time of inclusion and randomization, baseline medical history, obstetric history, and laboratory work up (hemoglobin, renal function (eGFR), CA-125, Anti-Mullerian hormone (AMH) in a subset of centers) are reported in the eCRF. The imaging characteristic displayed in Table 1 will all be registered.

Patients will fill out validated Health-Related Quality of Life (HRQOL) and symptom questionnaires (see "outcome measures")

### Procedure

At procedure, data about the course of the intervention (UAE or operation), any particularities or complications are reported in the eCRF. At discharge from the hospital the eCRF will report the total of admitted days and complications during hospital stay.

### Follow-up

The research investigator will send invitations for the digital online secured patient questionnaires by email at baseline, 6 weeks, 3 months, 6 months, 12 months and 24 months of follow-up. All patients will also specifically be asked at baseline to give their consent to be approached for long-term follow up. Validated questionnaires will be filled out to report on HRQOL, symptoms, clinical outcomes, return to normal activities, absence of work, medication use, costs, medical consultation/consumption, and additional received therapy (see “outcome measures”). The patients who underwent UAE will receive a TVUS at 6 weeks and 6 months with an MRI at 6 months to compare the adenomyosis features with baseline results. In the hysterectomy group, pathology outcomes are also registered. All the eCRFs will report complications.

### Outcomes measures

The primary outcome is quality of life at 6, 12 and 24 months after index procedure as measured by a combination of the World Health Organization Quality of Life Scale (whoqol-Bref) and Short Form-12 (SF-12) Questionnaire.

Secondary outcomes at 6 weeks and 3, 6, 12, 24 months after treatment consists of:

Clinical outcomes: technical failure rate, clinical failure arte as defined by secondary hysterectomy, additional therapy or reinterventions, complications.Recovery related outcomes (6 weeks, 3 and 6 months): hospital stay, return to normal activities (Recovery Index-10).Symptom and quality of life outcomes: menstrual characteristics (pictorial blood assessment chart), validated pain-questionnaire (Numeric Pain Rating Scale 0-100 scale, Facet 1: Pain and discomfort WHOQOL-100), sexual functioning (WHOQOL-100, sexual activity domain), satisfaction (Likert-scale, vignettes preference), quality of life (WHOQOL-Bref, SF-12).Cost utility analysis (European Quality of Life 5 Dimensions) after 12 months.Laboratory outcomes (baseline, 6 weeks and 6 months): hemoglobin, CA-125 and AMH in specific predefined centers.Pathology outcomes (6 weeks): pathological finding of uterus in hysterectomy group.

Also, imaging outcomes will be investigated in order to identify potential predictive parameters for therapy effect.

TVUS (baseline, 6 weeks and 6 months): imaging parameters described in Table 1, uterine size reduction and reduction of fibroid volume in case of concomitant fibroids. In specific predefined centers, we will measure vascular index (3D power Doppler).MRI (baseline and 6 months): imaging parameters described in Table 1, uterine size reduction, junctional zone reduction, infarction rate, reduction of fibroid volume in case of concomitant fibroids, presence of endometriosis.

### Sample size

This study has a noninferiority design, where UAE is considered noninferior to hysterectomy when HRQOL at 6 months does not differ (delta) more than 5 points (scale 0-100). When the following assumptions are used: SD of 9 points (scale 0-100), alpha 0.10, power 0.80, using a one-sided two-sample equal-variance *t* test, a sample size of 1 x 52 patients (embolization) and 1 x 34 patients (hysterectomy) is needed. Excluding 10% dropout, in total 96 patients are needed for the primary outcome. Assumptions are based on the Embolization versus Hysterectomy (EMMY) trial outcomes [13].

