### Statistical analysis

Analysis of the study will be based on the intention-to-treat and per protocol analysis. With regard to the primary outcome variable (WHOQOL-Bref, SF-12), non-inferiority is established between UAE and hysterectomy when the mean difference does not exceed 5 points (with a SD of 9 points).

The primary outcome will be analyzed using linear mixed modeling, applying transformation if necessary, adjusting for, if necessary, clinically relevant baseline imbalances. With regard to the secondary outcomes, we will use the appropriate nonparametric and parametric statistics to evaluate statistically significant differences between the two treatments. A *P* value <.05 will be considered as statistically significant. In all analyses, statistical uncertainties will be expressed in 90%CI.

The database will be locked 6 months after the last surgical procedure in order to obtain the short-term outcomes. These data will be analyzed and published in a “short term results” manuscript. The long-term results (HRQOL and costs) will be analyzed 12 months after the last procedure, when the last patient returned her last questionnaire.

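### The 52 + 34 sample size does not fit the stated one-sided alpha of 0.10 or the 2:1 randomisation, so the error level of the non-inferiority test is ambiguous and the arm targets do not match the design

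*Protocol article*

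**What the plan says.** All references are to the protocol article.

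- **Sample size**, the criterion: "UAE is considered noninferior to hysterectomy when HRQOL at 6 months does not differ (delta) more than 5 points". The SD is 9 on the same 0-100 scale.
- **Sample size**, the test: "alpha 0.10, power 0.80, using a one-sided two-sample equal-variance" *t* test.
- **Sample size**, the result: "a sample size of 1 x 52 patients (embolization) and 1 x 34 patients (hysterectomy) is needed", followed by "Excluding 10% dropout, in total 96 patients are needed for the primary outcome".
- **Abstract, Methods**: "patients will be randomly allocated to treatment in a 2:1 UAE versus hysterectomy ratio". The section on procedures, recruitment and randomization repeats the 2:1 ratio.
- **Statistical analysis**: "statistical uncertainties will be expressed in 90%CI", for all analyses. Non-inferiority is described there as a mean difference within 5 points. The text does not say which confidence bound is compared with the margin.

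The article states no assumed true difference between the arms and does not explain the 52:34 split.

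**The concern.** Two things do not fit together.

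First, the error level. A one-sided test at 0.10 corresponds to a bound of a two-sided 80% interval. A bound of a two-sided 90% interval is a one-sided test at 0.05. The sample size paragraph names the first level and the analysis section implies the second. In a non-inferiority trial this level decides whether the claim is made, so a reader should not have to choose between two sections.

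Second, the arm sizes. A calculation for a 2:1 trial should give arms in the ratio 2:1, and these do not. If 34 evaluable hysterectomy patients are really required, 96 patients randomised 2:1 would not be expected to provide them.

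**Working it through.** **Inputs.** Margin 5, SD 9, one-sided alpha 0.10, power 0.80, arms 52 and 34, dropout 10% and total 96 (Sample size). Allocation 2:1 (Abstract; procedures, recruitment and randomization). Interval level 90% (Statistical analysis). True difference 0: my assumption, as none is stated.

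**Formula.** For the one-sided equal-variance *t* test, SE = 9 × √(1/n₁ + 1/n₂), noncentrality = 5/SE and df = n₁ + n₂ − 2. Power is the probability that a noncentral *t* exceeds the central critical value.

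**Step 1: the plan's own arms.** For 52 + 34, SE = 9 × √(1/52 + 1/34) = 1.985, noncentrality = 5/1.985 = 2.519 and df = 84.

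| One-sided alpha | Critical *t* | Power |
|---|---|---|
| 0.10 (as stated) | 1.292 | 0.890 |
| 0.05 | 1.663 | 0.803 |

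Solving instead for 80% power at the plan's own ratio, 52/34 = 1.53, gives 39 + 25 = 64 at one-sided 0.10 and exactly 52 + 34 = 86 at one-sided 0.05.

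**Step 2: the total.** 86/0.9 = 95.6, rounded up to 96. The dropout inflation is correct.

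**Step 3: the allocation.** At 2:1, 96 × 2/3 = 64 and 96 × 1/3 = 32, and 32 is below 34 before any dropout. After 10% dropout, 64 × 0.9 = 57.6 and 32 × 0.9 = 28.8, or about 58 + 29.

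**Step 4: what a 2:1 calculation gives on the stated inputs (*t* test).**

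| One-sided alpha | Evaluable for 80% power |
|---|---|
| 0.10 | 46 + 23 = 69 |
| 0.05 | 62 + 31 = 93 |

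Neither total is 86.

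**Step 5: power of the design as randomised.**

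| Arms | One-sided 0.05 | One-sided 0.10 |
|---|---|---|
| 64 + 32 (no dropout) | 0.817 | 0.899 |
| 58 + 29 (10% dropout) | 0.782 | 0.875 |
| 57 + 29 (10% dropout, other rounding) | 0.780 | 0.873 |

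**Step 6: what the choice of level does to the decision.** With 58 + 29 and SD 9, SE = 2.05. The one-sided bound lies 1.292 × 2.047 = 2.64 points from the estimate at 0.10, and 1.663 × 2.047 = 3.40 points at 0.05. UAE is therefore declared non-inferior for an observed deficit of up to 5 − 2.64 = 2.36 points at 0.10, but only up to 5 − 3.40 = 1.60 points at 0.05. An observed deficit between about 1.6 and 2.4 points passes at one level and fails at the other.

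**The case against.** **The analysis section already settles the level.** It prescribes 90% intervals for every analysis, which amounts to one-sided 0.05, and no section mentions an 80% interval. A reader might infer that the primary claim will be tested at twice its proper error rate. The documents do not support that. They show two sections in conflict, with the analysis section pointing to 0.05. The conflict still stands, because that section never links a confidence bound to the margin, and the only alpha given expressly for the one-sided comparison is 0.10.

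**A non-zero true difference could explain 52 + 34 at alpha 0.10.** This is so: a true UAE deficit of about 0.8 points brings power at one-sided 0.10 down to about 0.80. So it cannot be said that only one-sided 0.05 reproduces the figures; that holds for a true difference of zero. No deficit is stated, however, and assuming one would not repair the allocation mismatch.

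**An equivalence calculation was meant.** Two one-sided tests at 0.10 give 52 + 34 a power of about 0.78 and need about 56 + 36 for 80%. The text also says noninferiority and one-sided.

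**The shortfall in the hysterectomy arm barely matters.** This largely stands. With no dropout, 64 + 32 has 82% power at one-sided 0.05, because the larger UAE arm compensates. A reader might infer from 32 against 34 that the trial is materially underpowered, and the figures do not show that.

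**Covariate adjustment will make up the difference.** The plan adjusts only if necessary, for clinically relevant baseline imbalances, and gives no correlation between baseline and outcome. No gain can be credited.

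**Conclusion.** The point holds as an internal inconsistency in stated numbers. For margin 5, SD 9 and a true difference of zero, 52 + 34 has 89% power at the stated one-sided 0.10 and 80% at one-sided 0.05. The likeliest explanation is that a two-sided 0.10 was written beside the word one-sided, but that is an inference for the sponsor to confirm. The 52:34 split contradicts the 2:1 allocation, and 96 patients at 2:1 are expected to give 64 + 32, or about 58 + 29 evaluable.

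The effect on power is small: about 2 points below target at one-sided 0.05 (0.78), and still above target at 0.10 (0.87). The main consequence is that the error level of the primary decision is not fixed without ambiguity. These figures assume that the achieved allocation matches the planned ratio and that dropout is 10% in each arm.

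**What to change.** Rewrite the Sample size paragraph and add one sentence to Statistical analysis:

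1. Confirm and state one alpha for the primary non-inferiority test. One-sided 0.05 is the level that reproduces the numbers. In that case, say that the relevant bound of the two-sided 90% interval is compared with the 5-point margin, and remove the one-sided 0.10.
2. State the assumed true difference (zero, if that was used).
3. Replace 52/34 with the figures that follow from 2:1: 96 randomised as 64 + 32, about 58 + 29 evaluable after 10% dropout.
4. Restate power as about 78% at one-sided 0.05. If the sponsor confirms one-sided 0.10 instead, the figure is about 87% and the interval level in Statistical analysis has to be changed to match.
5. Do not cite baseline adjustment as recovering the lost power.

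The cost is a text change with no new patients; the stated power falls from 80% to about 78%. If the sponsor prefers to keep 80% at one-sided 0.05, 93 evaluable patients are needed: 93/0.9 = 103.3, so 104 randomised, or 105 (70 + 35) in exact 2:1. The article says that analysis had not started at submission, so the level can be settled before results are known.

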### Statistical analysis

Analysis of the study will be based on the intention-to-treat and per protocol analysis. With regard to the primary outcome variable (WHOQOL-Bref, SF-12), non-inferiority is established between UAE and hysterectomy when the mean difference does not exceed 5 points (with a SD of 9 points).

The primary outcome will be analyzed using linear mixed modeling, applying transformation if necessary, adjusting for, if necessary, clinically relevant baseline imbalances. With regard to the secondary outcomes, we will use the appropriate nonparametric and parametric statistics to evaluate statistically significant differences between the two treatments. A *P* value <.05 will be considered as statistically significant. In all analyses, statistical uncertainties will be expressed in 90%CI.

The database will be locked 6 months after the last surgical procedure in order to obtain the short-term outcomes. These data will be analyzed and published in a “short term results” manuscript. The long-term results (HRQOL and costs) will be analyzed 12 months after the last procedure, when the last patient returned her last questionnaire.

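### The non-inferiority criterion compares the mean difference with 5 points and names no confidence limit, which contradicts the one-sided test behind the sample size

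*Protocol article*

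**What the plan says.** The Statistical analysis section of the protocol article gives the success criterion for the primary outcome: "non-inferiority is established between UAE and hysterectomy when the mean difference does not exceed 5 points (with a SD of 9 points". The Sample size section has a near-identical statement: "UAE is considered noninferior to hysterectomy when HRQOL at 6 months does not differ (delta) more than 5 points (scale 0-100".

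The Sample size section also sets out an inferential test. It assumes "SD of 9 points (scale 0-100), alpha 0.10, power 0.80", "using a one-sided two-sample equal-variance" t test, and concludes that "a sample size of 1 x 52 patients (embolization) and 1 x 34 patients (hysterectomy) is needed". For attrition it adds: "Excluding 10% dropout, in total 96 patients are needed for the primary outcome".

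The Statistical analysis section plans a linear mixed model for the primary outcome and 90% confidence intervals throughout. No sentence says that a limit of such an interval must lie inside the 5-point margin.

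**The concern.** A non-inferiority claim needs the data to rule out a deficit as large as the margin, so the quantity to compare with 5 points is a confidence limit. The article states the criterion twice and both times compares the difference itself. The 90% interval is given as a way to report uncertainty, with no role in the decision. The planning SD of 9 appears inside the rule, where it has no function once the trial has its own data.

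The 6-month HRQOL comparison carries the trial's main conclusion; the Discussion says that UAE could be offered as a less invasive alternative if it proves comparable. If the sentence were followed as it stands, an observed deficit of 4.9 points would count as non-inferior. A reader who assumes that a confidence limit was meant still cannot tell its level, because the Sample size section gives a one-sided alpha of 0.10 and the Statistical analysis section gives 90% intervals, which correspond to one-sided 0.05.

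**Working it through.** **Inputs.** From the Sample size section: margin 5, SD 9, alpha 0.10 described with a one-sided test, power 0.80, 52 UAE and 34 hysterectomy, 10% dropout, total 96. From the Statistical analysis section: 90% CI. Assumption: a true difference of 0 for power, which the article does not state.

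**1. Reproduce the sample size.** With allocation ratio r = 52/34 = 1.53, the hysterectomy arm needs n = (1 + 1/r) × SD² × (z₁₋ₐ + z₀.₈)² / margin².

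- One-sided 0.05: 1.654 × 81 × (1.645 + 0.842)² / 25 = 33.1, so 34; the UAE arm is 34 × 1.53 = 52. Total 86, and 86/0.9 = 95.6, so 96. This matches the article exactly.
- One-sided 0.10, as literally written: 1.654 × 81 × (1.282 + 0.842)² / 25 = 24.2, so 25; the UAE arm is 39. Total 64. This does not match.

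**2. Standard error at the planned numbers.** SE = 9 × √(1/52 + 1/34) = 1.985, with 84 degrees of freedom.

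**3. The rule as worded.** Let δ be the true UAE deficit. Then P(observed deficit ≤ 5) = Φ((5 − δ)/SE).

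**4. Confidence-limit rules.** The observed deficit must be below 5 − t × SE.

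- 90% CI (one-sided 0.05): 5 − 3.30 = 1.70 points.
- 80% CI (one-sided 0.10): 5 − 2.56 = 2.44 points.

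| True UAE deficit | As worded | 90% CI rule | 80% CI rule |
|---|---|---|---|
| 0 | 99.4% | 80.3% | 89.0% |
| 5 | 50.0% | 5.0% | 10.0% |
| 6 | 30.7% | 1.6% | 3.7% |
| 7 | 15.7% | 0.4% | 1.1% |

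The 80.3% and 89.0% come from the noncentral t distribution; the other entries use the normal approximation. In 200,000 simulated trials at a true deficit of 5, the three rules declared non-inferiority in 50.1%, 5.0% and 10.0%.

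**5. Example.** An observed deficit of 4.9 passes as worded, although the upper limit of its 90% CI is 4.9 + 3.30 = 8.2 points.

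**6. Sensitivity.** The 50% at the margin does not depend on the numbers of patients or the SD. The other figures shift little if 86 evaluable patients split close to the stated 2:1 allocation. With 57 and 29, SE is 2.05, the as-worded rule gives 31% at a deficit of 6 and 16% at 7, and power under the 90% CI rule is about 78.0%.

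**The case against.** The strongest reply is that no one plans to decide from a point estimate. The article names a one-sided t test with an alpha and a power, and it plans 90% intervals for all analyses. The planned 52 and 34 fit a 90% CI rule exactly, while the literal rule would have 99.4% power. The sentence may only restate the design hypothesis, with the difference meaning the true one; the SD in brackets, copied from the sample-size inputs, supports that reading. This stands in part: the intended test can largely be recovered. It does not remove the problem, because the only stated criterion omits the limit and the two sections imply different levels for it.

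Three stronger readings are tempting and should not be drawn:

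- **The trial has a 50% false non-inferiority rate.** That rate follows from the wording taken literally. The sample size points to a different rule, so it is not an established property of the design.
- **The rule would fail a UAE that is more than 5 points better.** The quoted sentences alone give no direction, but the Sample size section calls the design noninferiority and the test one-sided, which largely answers this.
- **It is an error that no deciding analysis set is named.** The article says only that "Analysis of the study will be based on the intention-to-treat and per protocol analysis". Which set decides is commonly left to the full protocol or SAP, which are not shown.

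**Conclusion.** The concern holds as a contradiction between the stated criterion and the stated design. Read literally, the criterion gives 50% false non-inferiority at the margin and 99.4% power at zero difference. The sample size rests on a one-sided test with 80% power, and 52 and 34 reproduce only at one-sided 0.05 (power 80.3%). A confidence-limit test was probably intended, but its level is not settled. The largest observed deficit that would pass is 5.0 points as worded, about 2.44 at one-sided 0.10 and about 1.70 at one-sided 0.05, so a result between 1.70 and 5 points could be called either way.

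These figures assume SD 9, the planned 52 and 34 evaluable patients, equal variances and, for power, a true difference of 0. They use a two-sample comparison; the planned mixed model may change the standard error.

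**What to change.** Replace the criterion in the Statistical analysis section with:

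> UAE is non-inferior if the lower limit of the two-sided 90% CI (one-sided alpha 0.05) for the 6-month mean difference, UAE minus hysterectomy, from the primary model lies above -5 points.

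Delete the SD of 9 from the rule, and bring the parallel sentence in the Sample size section into line.

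At the same time, reconcile the alpha of 0.10 with the one-sided test in the Sample size section. One-sided 0.05 is the level that reproduces 52 and 34 and fits the 90% CI. If one-sided 0.10 was truly meant, the deciding interval is an 80% CI, the plan must say so, and the stated numbers give 89.0% power and not 80%.

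**Cost.** Wording only, and no change in sample size. The article reports that analysis had not started at submission, so the change can be made before database lock. The downside is a stricter criterion than the literal wording: under the 90% CI rule the observed deficit must be below about 1.70 points, where the present sentence allows 5.
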